### Additional Data

Patients’ characteristics (age, sex, place of residence, baseline lung function, allergies, comorbidities, type of medication, etc) will be recorded. The effect of these parameters on the pattern of lung function variability will also be explored.

### Statistics

Normally distributed data will be presented as means (SD) and compared with Student’s *t* test, while nonparametric data will be presented as medians with ranges and compared with the Mann-Whitney *U* test. A chi-square or Fisher exact test will be applied to compare different frequencies between the study groups. Multivariable linear regression analyses will be used to explore the effect of various parameters on lung function variability. All analyses will be performed with MatLab and SPSS software (version 25.0; IBM Corp).

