## Methods

### Study Objectives and Hypotheses

The first objective of the study (objective 1) is the assessment of lung function variability in healthy children and adolescents, focusing on the range and pattern of short- and long-term fluctuations of PEF and FEV1 and the parameters that may influence them. The second objective (objective 2) is the assessment of lung function variability in children and adolescents with asthma; the pattern of short- and long-term PEF and FEV_1_ variability will be established and the differences from healthy subjects will be defined. Specific changes in the variability pattern prior to exacerbation will also be sought and described (objective 3).

We hypothesize that healthy children and adolescents present normal short- and long-term variability of PEF and FEV1, and that the pattern of variability is influenced by age, sex, and environmental stimuli (season, weather conditions, viral infections, etc). Significant lung function variability is also expected for children and adolescents with asthma; the patterns of variability in children and adolescents with asthma may differ from those observed in healthy children and adolescents, being also influenced by environmental conditions and treatment modalities (controller therapy) in a distinguishable way. Finally, we hypothesize that changes in the pattern of lung function variability occur prior to the loss of asthma control and, thus, may be used to predict the exacerbations of the disease.

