### Sample Size Estimation

Data regarding long-term PEF and FEV1 variability in children and adolescents (with or without asthma) are lacking. Based on lung function variability, data from adults with asthma [14], and assuming a maximum dropout rate of 10%, we estimated that a sample size of 200 children and adolescents (100 in each group) would allow us to detect a difference of at least 1% in PEF or FEV1 coefficient of variation (CV) between healthy participants and participants with asthma, with 90% power at the 0.05 level. Sample size estimation was performed using the G*Power software (version 3.1.6) [15] after assuming a nonparametric distribution of lung function parameters (Wilcoxon rank-sum test).

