### Lung Function Measurements

PEF and FEV1 measurements will be performed using an FDA-approved ultraportable spirometer (Spirobank Smart; MIR Medical International Research), with a bidirectional digital turbine (flow range ± 16L/s; volume accuracy ±3% or 50 mL; flow accuracy ±5% or 200 mL/s; dynamic resistance <0.5 cm H_2_O/L/s) and capable of connecting to a smartphone via Bluetooth using a dedicated freeware app (iSpirometry, MIR Medical International Research). Apart from PEF and FEV1, the device provides data on the forced expiratory capacity (FVC) and forced expiratory flow between 25% and 75% of FVC (FEF25-75). The app includes graphic incentives to assist in performing technically acceptable tests; it also includes a quality grading system that generates messages to inform whether the measurement was technically correct or, if not, the nature of the mistake (eg, “good blow” for an acceptable test, or “blow faster,” “blow longer,” etc, for nonacceptable maneuvers). Each participant will receive his personal spirometer, which will be paired to one or more smartphones (participant’s device, parents’ device, or both). In a case of two or more participants from the same family, each spirometer will be paired to a separate smartphone. Detailed information regarding use and maintenance of the device will be provided in the form of a printed brochure and online resources available on the study web site [17].

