### Variability Analysis

Participant-specific files will be used for variability analysis, focusing primarily on the variability of PEF and FEV1 and secondarily on FEV1/FVC and FEF25-75. All variables will be transformed into percentage predicted values according to GLI normative data [16].

Lung function variability will be assessed in 3 ways: (1) standard variability indices, (2) detrended fluctuation analysis (DFA), and (3) sample entropy (SampEn).

Standard variability indices such as CV (defined as SD divided by the mean) will be used. To avoid any bias due to the presence of trends within the time series, CV will also be calculated as the average of 24 moving windows (length 14 measurements; step 7 measurements).

DFA is a method that has been widely used for the investigation of intrinsic correlation within time series [19]. Initially, the square root of the time series F(*n*) is calculated for segments of different (time) length *n*. A linear relationship in the logarithmic graph F(*n*) - log(*n*) indicates the existence of fractal architecture in the scaling of the specific data, while the slope *a* of the line describes the pattern of long-term fluctuations [19]. A change in daily variability of PEF or FEV1 results in a simultaneous deviation from the predetermined *a* value [6]. This deviation can easily be detected and quantified. It has been shown that the magnitude of *a* deviation reflects the likelihood of asthma exacerbation within the next month [6].

SampEn is a measure of increased irregularity or complexity, which relies on the identification of recurrent patterns within a nonstationary time series (ie, the probability that a series of points within the signal will repeat themselves at a subsequent time-point) [20]. Within a regular and less complex system, the frequency of sequence matches is high; therefore, the entropy is low. SampEn has emerged as a more reliable index of dynamic variability, mainly because it is relatively independent of the length of the time series [20].

Variability analysis will be performed in the MatLab environment.

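### The healthy-asthma comparison (objective 2) is planned and powered as an unadjusted two-sample test, although the cohorts are nonrandomized, unmatched as described and measured in different calendar periods

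*Protocol article*

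**What the plan says.** All references are to the protocol article.

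- **Group comparison.** Statistics gives two-sample tests for continuous data: "Normally distributed data will be presented as means (SD) and compared with" Student's *t* test, and "nonparametric data will be presented as medians with ranges and compared with the Mann-Whitney" *U* test. Neither takes covariates.
- **Sample size.** The 200 children (100 per group, 10% dropout, 90% power, 0.05 level) are meant to "detect a difference of at least 1% in PEF or FEV1 coefficient of variation (CV) between healthy participants and participants with asthma". The calculation was done "after assuming a nonparametric distribution of lung function parameters (Wilcoxon rank-sum test").
- **Regression.** Statistics adds: "Multivariable linear regression analyses will be used to explore the effect of various parameters on lung function variability". No group term and no covariates are named there. Additional Data lists age, sex, residence, baseline lung function, allergies, comorbidities and medication as characteristics whose effects will be explored.
- **Expected influences.** Study Objectives and Hypotheses expects, for healthy children, that "the pattern of variability is influenced by age, sex, and environmental stimuli (season, weather conditions, viral infections, etc"). For children with asthma it names environmental conditions and controller therapy.
- **Design and timing.** Study Design calls the trial nonrandomized with two study groups. Both cohorts are aged 6-18, and no matching is described. Under the Protocol heading, healthy children are measured in Phase I (January-September 2020) and children with asthma in Phase II (October 2020-December 2021).

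**The concern.** The contrast between healthy children and children with asthma carries objective 2 and is the only one for which the study is powered. In a nonrandomized comparison, an unadjusted test attributes every systematic difference between the groups to the disease. The investigators expect age, sex and season to affect the outcome, so they have named candidate confounders of their own comparison. The design does nothing to balance them: age is restricted to a 12-year span but not matched, sex is free, and season is partly tied to group by the schedule.

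The target difference is 1 point of CV. A shift of a few tenths of a point from age mix or season would be a large fraction of it. It could produce a significant result without any asthma effect, or hide a real one if it ran the other way.

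**Working it through.** **1. The plan's own figure.** The SD of CV is not given (it comes from an adult asthma source), so 100 per group cannot be reproduced directly. It can be solved backwards.

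- Inputs from Sample Size Estimation: difference 1 (read as 1 percentage point of CV), power 90%, level 0.05, 100 per group, 10% dropout, hence 90 evaluable per group.
- Assumptions: two-sided test; efficiency of the rank-sum test relative to the t test 3/π = 0.955.
- SD = 1 / [(1.960 + 1.282) × √(2 / (90 × 0.955))] = 1 / (3.242 × 0.1525) = 2.02.
- Forward check with SD 2.0: the t test needs 2 × (3.242 × 2.0)² = 84.1, so 85 per group. Then 85 / 0.955 = 89.0, so 90. Then 90 / 0.9 = 100.

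The stated size therefore fits an unadjusted two-sided rank-sum test with an SD near 2.0. A one-sided test would imply 2.24.

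**2. False-positive rate when a non-asthma shift is present.** Assume no asthma effect but a shift of *b* points in CV from other causes.

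- SE = 2.0 × √(2 / (90 × 0.955)) = 0.305.
- Rejection rate = 1 − Φ(1.960 − b/SE) + Φ(−1.960 − b/SE).

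| b (points) | b/SE | SD 2.0 | SD 1.5 | SD 3.0 |
|---|---|---|---|---|
| 0.2 | 0.66 | 10% | 14% | 7% |
| 0.4 | 1.31 | 26% | 42% | 14% |
| 0.6 | 1.97 | 50% | 75% | 26% |

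The b/SE column is for SD 2.0. The last two columns use SE 0.229 and 0.458 and show how far the answer depends on the unstated SD.

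**3. What adjustment does.** This simulation had 90 per group, residual SD 2.0, age SD 3 years clipped to 6-18, no asthma effect, and 1,500 runs per setting. The age gap and slope are assumptions. Entries are rejection rates for Mann-Whitney / for regression on group and age.

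| Mean age gap | 0.1 point per year | 0.25 point per year | 0.4 point per year |
|---|---|---|---|
| 0 years | 5% / 6% | 5% / 4% | 5% / 5% |
| 1 year | 5% / 4% | 10% / 6% | 19% / 5% |
| 2 years | 10% / 5% | 29% / 5% | 56% / 6% |

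The unadjusted test drifts with the imbalance; the adjusted one stays near 5%.

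**4. Does percent-predicted scaling already adjust?** Variability Analysis converts all values to percent predicted. For one child over 90 days the predicted value is nearly a constant *k*, and CV = (SD/k) / (mean/k) = SD/mean. A numerical check gave 0.0711 before and after scaling. An effect of age or sex on CV therefore passes through. The same holds for the DFA slope: a constant factor shifts the log-log line without changing its slope.

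**5. Season and period.** Phase I covers at most January-September of one year. Phase II covers 15 months, of which October-December (twice, so 6 of 15) has no healthy counterpart. Season is partly tied to group, and calendar period is fully tied to it.

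**The case against.** The strongest reply is that adjustment is left open rather than ruled out. A multivariable regression on variability is planned, age and sex are recorded, nothing bars a group term, and a journal article may leave covariate lists to a fuller plan. It stands that the list of covariates alone would not be a finding. The reply does not remove the point, because the article does fix the test for comparing groups and powers the study on it. It gives the regression a different purpose.

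The size is also fairly challenged. The documents give no SD of CV, no age distribution and no seasonal effect, so the error rates above are conditional illustrations.

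A reader might infer more than the documents support:

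- *That age, sex and season are known to drive variability.* The text states a hypothesis, and its age and sex part concerns healthy children.
- *That one value per child is a flaw, or makes the environmental hypothesis untestable.* One index per child avoids treating 180 readings as independent. Children measured in different months still allow a between-child test of season. The window average ("CV will also be calculated as the average of 24 moving windows (length 14 measurements; step 7 measurements") is an additional summary, and nothing says that dates or window values are discarded.
- *That siblings invalidate the tests.* The only basis is a device instruction ("In a case of two or more participants from the same family, each spirometer will be paired to a separate smartphone"). No number of siblings or correlation is given.
- *That adjustment is worth 25% more children.* That figure (1/0.8 = 1.25) assumes that covariates explain 20% of variance and are balanced between groups. With ages uniform over 6-18 (variance 12²/12 = 12) and a 2-year gap, R² of age on group is 1/13 = 0.077. The variance inflation is 1/(1 − 0.077) = 1.083, and the gain falls to 1/(0.8 × 1.083) = 1.15. Neither input is in the documents.

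**Conclusion.** The point holds as a weakness in a stated analysis choice. Objective 2 rests on an unadjusted comparison of nonrandomized cohorts that share only an age range and are measured in different periods, for an outcome that the plan expects to vary with age, sex and season. Neither the exploratory regression nor percent-predicted scaling closes the gap.

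The mechanism follows from the text; the size does not. Rates of about 10%, 26% and 50% for shifts of 0.2, 0.4 and 0.6 point assume a two-sided rank-sum test, 90 per group and an SD of about 2.0 that the protocol does not state. Whether such a shift will occur is unknown.

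It would also be wrong to infer that a season or month term cures the problem. Such a term is informed about group only by the months common to both phases, and no model can separate group from calendar period in this design.

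**What to change.** Before asthma data are collected, state in Statistics that the objective 2 estimate is the group coefficient with its 95% CI from a linear regression of each per-child index: CV (log-transformed if skewed), DFA slope and SampEn. The terms should be group, age, sex, and season or month of measurement, plus recruitment site type if the cohorts overlap on it. Keep the Mann-Whitney test as a descriptive, unadjusted comparison. A more elaborate window-level mixed model is possible but is not needed to meet this point.

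Add a limitation: calendar period is fully tied to group, and seasonal adjustment rests only on the months of the year that both phases share.

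The cost is a few sentences and slightly more analysis work. Age and sex are already recorded, and measurements are filed by date and time. The timing allows it, since Phase II is scheduled to start in October 2020 and only healthy children are reported as enrolled as of June 2020. The downside is that the headline test becomes model-based rather than rank-based, so residuals and the choice of scale need checking.

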## Results

The study is funded by the “C. Caratheodory” Programme of the University of Patras, Greece (PN 47014/24.9.2018). It was approved by the Ethics Committee (decision 218/19-03-2019) and the Scientific Board (decision 329/02-04-2019) of the University Hospital of Patras, Greece.

Patient recruitment commenced in January 2020, and the trial is scheduled to end in January 2022. As of June 2020, 100 healthy children have been enrolled (74 of them have completed the measurements). The anticipated duration of the study is 24 months. The first part of the study, the assessment of lung function variability in healthy children and adolescents, will be completed in August 2020, and the results will be available for publication by October 2020.

Access to the study dataset will be limited to the investigators. After the analysis and publication of the results, the study database will be made available by the corresponding author upon reasonable request. Results will be published in peer-reviewed journals and will be presented in relevant conferences. Authorships will follow the Vancouver declaration.

## Discussion

Increased lung function variability correlates with the frequency of respiratory symptoms in the general population [21] and is indicative of poor asthma control in patients with asthma [7-9,14].

Frey et al [6] applied DFA on 300 consecutive PEF values from a cohort of adults with asthma treated in a crossover manner with regular short-acting beta-2 agonists (SABA), regular long-acting beta-2 agonists (LABA), or placebo. They showed that long-term PEF variability was increased in the SABA phase, which meant that there were several periods of decreased lung function (increased vulnerability and high probability of exacerbation). Conversely, PEF variability was decreased during the LABA phase, signifying that lung function remained persistently within normal limits (decreased vulnerability and low probability of exacerbation). Thamrin et al [8] showed that the self-similarity of PEF values over time correlates well with the loss of asthma control within two weeks following the withdrawal of inhaled corticosteroids. Their findings were later corroborated by Kaminsky et al [14] in a large clinical trial of adults with asthma under controller therapy. Thamrin et al [22] have also demonstrated that the probability of asthma exacerbation at the individual level can be estimated by combining the autocorrelation properties of PEF over time with the absolute PEF value at a specific time point, indicating that both are significant for predicting a loss of disease control in the near future.

Regarding SampEn, Veiga et al [23] found that the entropy of airflow time series was reduced in subjects with asthma compared to healthy controls; lower entropy was associated with more severe airflow obstruction (forced oscillations technique) in that study. More recently, Dames et al [24] investigated the entropy of airflow in patients with chronic obstructive pulmonary disease (COPD) and reported that the SampEn of airflow during resting breathing decreased in proportion to the degree of airway obstruction. Similar data in children and adolescents with or without asthma are lacking.

To remain stable yet adaptable to change, any physiological system needs to balance between order and chaos [25]. Asthma appears to be associated with increased order (reduced complexity) and increased variability of lung function, resulting in wide fluctuations that may lead to periods of increased vulnerability and reduced adaptability to a changing environment [26]. From a clinical standpoint, these features translate into more frequent exacerbations and poor control of the disease. Thus, when properly quantified, changes in lung function over time may reflect both past and future control of asthma [26].

Healthy children and adolescents may present normal short- and long-term fluctuations in lung function; the pattern of this variability may be influenced by age, sex, and environmental conditions. Significant lung function variability may also be present in children and adolescents with asthma, but the patterns may differ from those observed in healthy children and adolescents. Such data would improve our understanding regarding the chronobiology of asthma and may permit the development of integrated tools for assessing the level of control and risk of future exacerbations.

## Abbreviations

COPD: chronic obstructive pulmonary disease
CV: coefficient of variation
DFA: Detrended Fluctuation Analysis
FEF25-75: forced expiratory flow between 25% and 75% of FVC
FEV1: forced expiratory volume at 1 second
FVC: forced expiratory capacity
GLI: Global Lung Initiative
LABA: long-acting beta-2 agonists
PEF: peak expiratory flowSampEn: Sample entropy
SABA: short-acting beta-2 agonists
